**Genetic analyzes**

Each participant will be asked to provide a voluntary saliva sample which is then analyzed with respect to the previously mentioned polymorphisms. Participants will be sent a coded test tube which is adapted for mail handling (Oragene, see [http://www.dnagenotek.com](https://mail.liu.se/owa/redir.aspx?C=c770dbacb4d543a68289873d76df6c57&URL=http%3a%2f%2fwww.dnagenotek.com)) subsequently videaresänds to [name] of Gothenburg University for analysis. Information about individuals' identities will not be enclosed these samples. Saliva samples will be stored in a biobank in the pharmacological department, the Department of Neuroscience and Physiology, Sahlgrenska Academy, Göteborg University, which also analyzes will be carried out. The management of the genetic material will follow our previous genetic studies of social phobia which has been approved by the Ethics Committee (see, eg, Ref 2004: M-416 and 421-2007-2223, the latter from the ethical review board in Stockholm).

**Evaluation**

Posttreatment measurements are made in connection with the final module completed. Follow up with a short phone interview and form occurs after 12 and 24 months. The latter is done to evaluate the longer-term treatment effects and to compare these with the short-term effects. Pre-, post-and follow-up measurements will be made with established international form (see above). An attempt will be made to try to identify predictors of treatment success and factors that may predict which individuals this type of treatment is best suited for.

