**Design**

Two hundred and fifty people diagnosed with social phobia in an experimental study be randomized into two treatment groups: 1) Internet-based CBT (n = 125) or 2) Control group who participate in a moderated discussion forum on the web (n = 125). The control group will be treated with Internet-based CBT after the initial group has completed their treatment, ie. after nine weeks. Genotyping based on saliva samples is done before starting treatment for those who leave the voluntary sample.

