**Screening, pretreatment assessment and randomization**

The screening process will follow the procedures from our recent study in the SOFIE project (No. 2005:187). When the subject has expressed an interest, a code is sent out which gives access to the portion of the site on which the screening instruments available. The participant answers the first forms: Social Phobia Screening Questionnaire-SPSQ (3) and Montgomery Asberg Depression Rating Scale-MADRS (24). Participants must meet the criteria for social phobia using the international classification system Diagnostic and Statistical Manual of Mental Disorders, 4th edition (DSM-IV) (25). This is mainly determined by SPSQ form that has been shown to have good sensitivity and specificity in comparison with the structured diagnostic interviews. In addition, we include a telephone screening, which follows a structured clinical interview, Structural Clinical Interview for DSM-IV - Axis I Disorders: SCID I (26). Individuals with current major depression and / or suicide-prone persons will be excluded from the study. Furthermore, the subject will be asked to submit a signed consent form to the research group. The constent form involves consent to do genetic analyzes and stores saliva samples in a biobank, the processing of personal data concerning him / her in accordance with the Data Protection Act and that he / she hs received information on the website about how the study.

The subjects meeting the inclusion criteria will then be randomized into two groups so that half may begin directly with the Internet-based self-help treatment program (treatment cycle 1) while the other half gets allocated to the control group which involves participation in a moderated discussion forum on the Internet for nine weeks after which they are treated as usual with the Internet-based program (treatment session 2). The latter group controls in this manner for the time and measurement.

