Before the treatment groups may have access to self-help program will fill the subjects in the pretreatment measures consisting of: Social Interaction Anxiety Scale (27), Social Phobia Scale (27), Liebowitz Social Anxiety Scale-LSAS (28), Beck Anxiety Inventory (29), and Quality of Life Inventory (30). All these forms are internationally established and have been shown to have good psychometric properties. Two handwritten forms, which measures the degree of alliance respectively. knowledge acquisition will also be designed and administered during the study period.

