**Treatment**

Treatment will be through the Internet in two rounds, and will take advantage of our previously developed structured self-help program that lasts for a total of nine active treatment weeks. The guided self-help program is based on an updated version of the previously used in our approved studies (Ref: 02-555, 03-636, 2004: m-163, 2005:187) ie. on well-proven principles from cognitive behavioral therapy. Following each treatment week participants will be asked a number of questions and send answers via the website to show that they have assimilated the module content. In connection with this they will obtain the password to the next module. Each week, participants also fill in LSAS form and question 9 from MADRS dealing with the zest for life and possible suicidal thoughts. This weekly measurement helps to monitor participants' current state and intervene if needed. All participants will be participate in Internet discussion group where they can speak and send messages to each other. The different treatment groups will have separate discussion groups, which are monitored daily. The degree of anonymity determines the participants themselves, and they may for example choose the username of your choice. The study coordinators will be available to answer questions.Psychology Candidates during the final phase of their education will, according to a well-established model, participate in the project in connection with their MSc theses. As in our previous treatment studies (10-12) they will serve as e-mail therapists under supervision. We have previously evaluated the efficacy of CBT program administered in this way in five randomized controlled trials, of which three have so far been published (10-12) along with an open study (31).

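### Post-treatment measurement is tied to finishing the last module in the CBT arm and only implied at nine weeks in the control arm, so outcome timing and availability can depend on adherence

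*Protocol*

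**What the plan says.** The Evaluation section states that "Posttreatment measurements are made in connection with the final module completed". It gives no week or window, and no instruction for a participant who does not reach the final module.

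The Treatment section describes a programme that "lasts for a total of nine active treatment weeks". After each treatment week participants answer questions and submit them through the website, and "In connection with this they will obtain the password to the next module".

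The Design section says that "The control group will be treated with Internet-based CBT after the initial group has completed their treatment, ie. after nine weeks". The section on screening, pretreatment assessment and randomization describes the control condition as "participation in a moderated discussion forum on the Internet for nine weeks after which they are treated as usual with the Internet-based program", and adds that this arm accounts for time and for measurement. It gives no assessment date for controls.

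The Treatment section also has a weekly measure: "Each week, participants also fill in LSAS form and question 9 from MADRS". Its stated purpose is safety and follow-up: "This weekly measurement helps to monitor participants' current state and intervene if needed".

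**The concern.** In a randomised comparison, the outcome should be sought from everyone at the same time after the start, whatever happens to their treatment. Here the written trigger is an adherence event that only one arm can experience during the comparison period. If it is applied as written, the CBT outcomes come from people who finished, on the dates they finished, while the forum outcomes come from whoever is approached at about nine weeks. Finishing a self-help programme is plausibly related to improvement, so the arms would no longer be compared like with like.

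This is a rule about data collection. An analysis plan can choose how to treat missing values, but it cannot recover questionnaires that were never requested or realign those collected at different times. The analyses of CBT response by genotype and of predictors of outcome draw on the same post-treatment measure.

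**Working it through.** The protocol has no figure to reproduce on this point. It mentions a power calculation but gives no effect size, SD, alpha, power, dropout or completion rate. The check is therefore mainly textual.

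**Step 1. Apply the two rules to each kind of participant.** The Evaluation section uses the final module; the Design and screening sections use nine weeks.

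| Participant | Final-module rule | Nine-week reading |
|---|---|---|
| CBT, on pace | about week 9 | week 9 |
| CBT, slow | later than week 9 | week 9 |
| CBT, stops submitting | trigger never reached | week 9 |
| Control, before crossover | no modules, so no trigger | week 9 |

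The rules agree only in the first row. The Design section treats the end of the first group's treatment and nine weeks as one event, but submission-dependent release of modules does not guarantee that.

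**Step 2. Does another provision fill the gap?** The weekly LSAS could supply a score near week 9. However, it is described for monitoring, and the protocol does not say whether controls, or CBT participants who have stalled, complete it. It would also not supply the Social Interaction Anxiety Scale, Social Phobia Scale, Beck Anxiety Inventory or Quality of Life Inventory. The statement that the control arm accounts for time and measurement shows an intention to measure controls over the same period, but sets no date.

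**Step 3. What the size could be, under assumptions only.** Inputs: 125 per arm (Design and Subjects sections). Assumed: SD = 1, two-sided 5% test, a share *m* of the CBT arm unmeasured and omitted from the comparison, all controls measured, and unmeasured CBT participants worse than completers by *g* SD.

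- If completers have mean benefit *C*, the whole-arm mean is (1 − m)·C + m·(C − g) = C − m·g. A completers-only mean is therefore too favourable by **bias = m·g**.
- SE = √(1/(125(1 − m)) + 1/125).
- Error rate when there is no true difference = Φ(bias/SE − 1.96) + Φ(−bias/SE − 1.96).
- Difference detectable with 80% power = (1.96 + 0.84)·SE.

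| m | g (SD) | Bias (SD) | Nominal 5% becomes | Detectable difference (SD) |
|---|---|---|---|---|
| 0 | any | 0 | 5% | 0.354 |
| 10% | 0.25 | 0.025 | 5.4% | 0.364 |
| 20% | 0.50 | 0.10 | 11.6% | 0.376 |
| 40% | 0.75 | 0.30 | about 54% | 0.409 |

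Worked case, m = 20% and g = 0.5: SE = √(1/100 + 1/125) = 0.134; bias/SE = 0.10/0.134 = 0.745; error rate = Φ(−1.215) + Φ(−2.705) = 0.112 + 0.003, or about 11.6% before rounding.

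The loss of precision is modest; the bias is the larger issue. Late measurement of slow participants is a further effect that this calculation does not model.

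**The case against.** The strongest reply is that the nine-week anchor is already in the protocol. The programme lasts nine weeks with questions after each week, the Design section places the end of the first group's treatment at nine weeks, and the control period is fixed at nine weeks with a stated aim of accounting for time and measurement. Read together, the Evaluation sentence may simply mean the end of the programme. Weekly LSAS scores are also planned. The genetic questions are listed as the primary issues, with the CBT-versus-forum comparison added afterwards.

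Much of this stands, and it rules out several stronger readings that a reader might be tempted by:

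- *That CBT non-completers are excluded.* No sentence says they are not approached or are left out of the analysis. How they are analysed may be set in a statistical analysis plan that is not shown.
- *That controls have no assessment before crossover.* The nine-week period and the aim of matching measurement imply that they do.
- *That baseline is collected after randomisation, or at week 9 for controls.* The wording "Before the treatment groups may have access to self-help program will fill the subjects in the pretreatment measures" sets a latest time for the forms. The section heading puts pretreatment assessment before randomisation, and the order of paragraphs proves nothing.
- *That the effect is overstated by some definite percentage.* Any such figure needs a completion rate and effect sizes that the protocol does not give.
- *That the genetic findings are distorted.* They use the same outcome, but nothing in the protocol links genotype to completion.

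What the reply does not remove is that the one explicit collection rule names module completion, and that the nine-week alternative has to be inferred from other sections.

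**Conclusion.** The point holds in a limited form. The protocol defines the post-treatment measurement by an adherence event in the CBT arm and leaves it implicit at nine weeks in the control arm. Followed literally, slow CBT participants are measured late and non-completers may go unmeasured, which can bias the randomised comparison. If those who stop do worse than those who finish, the bias favours CBT.

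The size cannot be determined from the protocol. Under the assumptions above it runs from 0.025 to 0.30 SD. These figures require that non-completers have no usable outcome and are omitted; they fall to zero if everyone is in fact measured at nine weeks, and weekly LSAS could reduce them for that scale. The conclusion that the sections need reconciling rests on the text alone and does not depend on these figures.

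**What to change.** Reconcile the Design, screening, Treatment and Evaluation sections by replacing the Evaluation sentence with a date-based rule, for example:

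*The full post-treatment battery is requested from every randomised participant in both arms at the same calendar time point, the end of the nine-week period counted from the common start of the treatment and control period, whatever the number of modules completed. Controls complete it before they are given access to the programme.*

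Counting from the common start is safer than counting from randomisation, because the protocol does not say how long after randomisation treatment begins. It would also help to state whether the weekly LSAS is requested from controls and from CBT participants who have stopped submitting modules.

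The cost is one revised sentence and a small website change, so that the questionnaires are opened by date and not by module. The estimated effect may be slightly less favourable, because participants who did not finish would contribute to it.

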**Schedule**

A total period of 6 months (August 2008 - January 2009) will be required for the selection, diagnosis, management of forms and saliva samples, treatment and initial analysis. The project will provide large amounts of data. In-depth analysis, as well as the compilation and writing of scientific reports, and will therefore last for a long time.

**Security**

The participant is recommended to get a free e-mail address with "Hushmail" that offers encryption (2048 bit) of the email. The service is operated by the company Hush Communications. All e-mails sent from Hushmail is kryperad and can not be traced. The encrypted e-mail correspondence will be via password-protected computers with topical definitions of antivirus software. The correspondence with clients will be printed and stored in purpose-designed covers. These, and other materials, will be tagged with an ID number and stored in a locked filing cabinet. When the retention period, according to the adopted standard, expired material will be destroyed. Data from the questionnaires will be recorded in anonymous form. This means that participants in the trials can not be identified afterwards. The results will also be analyzed at the group level.

**Privacy and genetic analyzes**

To protect participants' identity will be samples and data to be encoded. All information will be kept strictly confidential and in accordance with the Data Protection Act. Code list, through which tube number will be linked to individual, will be kept locked up in the project at Uppsala University. The results of the analysis disclosed not to any other party, unless required by operation of law. Although the participant's family, doctors, insurers and employers included in the concept of "another party". The genetic results obtained are thus only for research. Participants may request a copy of analysreslutaten, as well as correction or that the sample be destroyed.

No individual data is traceable in the scientific reports presented from this study and the results will be reported as averages. The participant's identity can not be tracked by the results that are stored but this can only be identified with a special code. The samples will be stored for up to 15 years and then destroyed. Samples will not be used for any purpose other than that described here

**Ethical considerations**

The subjects participating voluntarily in the study. The study assumes that participants are informed that in the case of self-help any improvement requires active engagement.

The following ethical risks have been identified: the first is that participants in need of specialized medical investigations may be included. At the slightest suspicion of unclear etiology, participants will be asked to seek medical advice in the community. We will also provide information about self-help program is not suitable if you suffer from severe depression or suicidal thoughts.

The people who are excluded from the study may perceive this negatively. All individuals who are excluded will therefore have a recommendation on how and where to seek alternative treatment in the community, and in cases it deems appropriate, make recommendations on appropriate self-help literature. Participants will be randomly allocated to one of the two groups (treatment cycle 1 and 2). To provide the best scientific evidence is not allowed participants to choose a group and those who do not agree to this will therefore not be included in the study.

Participants in the control group had to wait for their treatment in nine weeks until the first group therapy is completed, which may be perceived as negative. While these individuals will be treated with Internet-based CBT and during the waiting time access to a moderated discussion forum.

To submit a saliva sample for genetic analysis can be seen as a possible privacy violation. They participate voluntarily and even participants who do not want to leave the test will be able to participate in treatment. Participants advised that anyone who works with the samples have to keep research data and results secret. Participants are informed of the results of the assays are not disclosed to any other party, including family, doctors, insurers or employers, unless required by operation of law. Information is also given that the genetic results are only for research and not used for any other purpose. As noted, all information will be kept absolutely confidential and the participant is assigned a personal code. Survey participants are offered ongoing opportunity to get answers to questions by telephone and encrypted e-mail during the study.

**Previous experience**

Extensive experience in similar studies in the project for both Internet-based therapy (10-13, 31) that genetic analyzes (20,22,23) of people suffering from social phobia.

**Significance**

The project can make important contributions to our understanding of how psychological treatment for SAD works. A particularly important question concerns the possibility of predicting treatment response based on genetic variation, which can have significant treatment implications. The results of the project will be significant for the understanding of social phobia, but also for other psychiatric disorder and mood disorders like depression where anxiety is an essential part of the symptomatology.

